# Explore Transplant at Home: a randomized control trial of an educational intervention to increase transplant knowledge for Black and White socioeconomically disadvantaged dialysis patients

**DOI:** 10.1186/s12882-015-0143-0

**Published:** 2015-08-28

**Keywords:** Kidney transplantation, Living donor, Racial disparities, African-Americans, Patient education, Health knowledge/attitudes, Transtheoretical model of behavioral change, Stages of Change

## Abstract

**Background:**

Compared to others, dialysis patients who are socioeconomically disadvantaged or Black are less likely to receive education about deceased donor kidney transplant (DDKT) and living donor kidney transplant (LDKT) before they reach transplant centers, often due to limited availability of transplant education within dialysis centers. Since these patients are often less knowledgeable or ready to pursue transplant, educational content must be simplified, made culturally sensitive, and presented gradually across multiple sessions to increase learning and honor where they are in their decision-making about transplant. The *Explore Transplant at Home* (*ETH*) program was developed to help patients learn more about DDKT and LDKT at home, with and without telephone conversations with an educator.

**Methods and Study Design:**

In this randomized controlled trial (RCT), 540 low-income Black and White dialysis patients with household incomes at or below 250 % of the federal poverty line, some of whom receive financial assistance from the Missouri Kidney Program, will be randomly assigned to one of three education conditions: (1) standard-of-care transplant education provided by the dialysis center, (2) patient-guided *ETH* (*ETH*-PG), and (3) health educator-guided *ETH* (*ETH*-EG). Patients in the standard-of-care condition will only receive education provided in their dialysis centers. Those in the two *ETH* conditions will receive four video and print modules delivered over an 8 month period by mail, with the option of receiving supplementary text messages weekly. In addition, patients in the *ETH*-EG condition will participate in multiple telephonic educational sessions with a health educator. Changes in transplant knowledge, decisional balance, self-efficacy, and informed decision making will be captured with surveys administered before and after the *ETH* education.

**Discussion:**

At the conclusion of this RCT, we will have determined whether an education program administered to socioeconomically disadvantaged dialysis patients, over several months directly in their homes, can help more individuals learn about the options of DDKT and LDKT. We also will be able to examine the efficacy of different educational delivery approaches to further understand whether the addition of a telephone educator is necessary for increasing transplant knowledge.

**Trial Registration:**

ClinicalTrials.gov, NCT02268682

## Background

In the United States there are approximately 637,000 patients with end-stage renal disease (ESRD) or kidney failure [1]. There are two options for ESRD patients to sustain life: dialysis or a kidney transplant from a deceased or living donor [1–4]. Kidney transplantation, especially living donor kidney transplant (LDKT), offers ESRD patients 6 to 16 additional years of life and improved quality-of-life compared to remaining on dialysis [1–3]. However, the majority of ESRD patients–450,000 as of 2013– still remain on dialysis. Although dialysis is life-saving, it only replaces 10-15 % of normal kidney function and can lead to cardiovascular disease, infection, and other complications [5, 6]. Additionally, the chance of a dialysis patient being alive after 5 years without a transplant is only 40 % [7]. Acknowledging its benefits over dialysis, the Centers for Medicare and Medicaid Services (CMS) has required that all dialysis patients receive transplant education and be informed of their option for transplant within 45 days of initiating dialysis.

In general ESRD patients who are Black and of lower socioeconomic status (SES) are significantly less likely to receive transplant education, pursue transplant evaluation, and receive deceased donor kidney transplants (DDKTs) and LDKTs [8, 9]. In fact, patients with kidney disease from low-SES neighborhoods experience higher mortality rates [10]. These patients may be more likely to have particular concerns about the costs of transplant medication [11], loss of disability benefits if they should receive a transplant [12], and limited access to adequate transportation to transplant appointments [13, 14]. Many low-SES patients may receive treatment at dialysis facilities with systemic barriers, including limited staff availability to provide education about transplant [15–17] or limited access to transplant education materials [18]. Without information about the risks and benefits of DDKT and LDKT, dialysis patients who do not present at a transplant center are often unable to make informed decisions about how best to treat their kidney disease [19, 20].

In light of these barriers, a 2014 American Society of Transplantation Consensus Conference recommended multiple ways to improve educational outreach for ESRD patients who have not yet presented at a transplant center [21]. These recommendations included repeating education multiple times and in settings prior to the transplant center, providing more culturally competent education at appropriate literacy levels, and using technology more effectively as an educational strategy. These approaches reflect a more general need to provide transplant education both consistently and gradually over time for patients who know less about it. Patients with significant barriers to learning about transplant also may benefit from support from a health educator, peer mentor, or social worker [22], including repeated discussions and more opportunities to ask questions about their transplant concerns.

Given the pressures on dialysis providers’ time [16] health insurance companies have incorporated the use of case managers or health educators within their organizations to distribute health information to patients via mail or over the telephone [23]. Some approaches that have been used to reach patients in clinical settings outside of dialysis centers involve mailing videos and print educational content at multiple time points to reach patients and their support networks when they are home [24], sending regular text messages to increase health knowledge and promote healthy behaviors [25, 26], and reinforcing educational content with a phone health educator [23]. These approaches have been shown to be effective in identifying patients with chronic illness early in the course of disease progression and intervening to increase knowledge of the best treatment options available, bridge the gaps in access to care, facilitate effective communication between the patient and providers, advocate on behalf of the patient, and plan for successful treatment outcomes in a high quality and cost-effective manner [27–29].

Applying these educational strategies to transplant education for the first time, we describe the protocol of a randomized control trial (RCT) with low-SES, Black and White dialysis patients comparing the efficacy of two versions of the *Explore Transplant at Home* (*ETH*) educational program with standard education being provided within dialysis centers. The three education conditions include: (1) standard-of- care education provided within dialysis centers; (2) a video-guided four-part *ETH* program delivered via mail, plus optional texts [*ETH* Patient-Guided (PG)]; and (3) a video-guided four-part *ETH* program with discussion facilitated by a transplant educator via telephone [*ETH* Educator-Guided (EG)]. We will compare whether these three educational approaches improve Black and White patients’ transplant knowledge, self-efficacy, and informed decision-making. We will also explore which DDKT and LDKT action steps patients commonly take during an 8 month period.

## Study Design and Methods

### Foundations of ETH

There is general consensus that interventions grounded in the best practices of behavioral change theories are more effective than those not based in theory [30]. Noting that many dialysis patients, especially racial minorities, are in early stages of decision-making to pursue transplant [8], there is critical need for an intervention that can meet patients where they are in this process and gradually increase knowledge, leading them towards making informed transplant choices. [name] and her team previously designed and tested the *Explore Transplant* (*ET*) program [19], a program grounded in the Transtheoretical Model of Behavior Change (TTM) [31]. The TTM holds that not all patients are ready to begin taking actions toward health behavior change, and that patients’ decision-making is impacted by their level of motivation, their weighing of the Pros and Cons, and their self-efficacy [31]. It has been successfully used to understand the decision-making of patients considering whether to engage in over 50 health behaviors [32–37], including decision making about organ donation [38, 39]. Through a group RCT, *ET* delivered face-to-face with patients while they were undergoing dialysis by transplant educators was shown to increase patients’ knowledge, informed decision-making, and pursuit of transplant [19]. As a result, the *Explore Transplant* program won the 2009 National Association of Transplant Professionals (NATCO) Quality of Care Award.

### Design and Advantages of Explore Transplant at Home

The original *ET* trial included four video and print educational modules: Exploring Transplant, Kidney Recipients’ Transplant Experiences, Living Donors' Donation Experiences, and Deciding What to Do. These modules were reviewed in person while the patients were undergoing dialysis within a one month period. Recognizing the significant barriers that disadvantaged dialysis patients face in pursuing transplant, the *ETH* modules were redesigned to be delivered by mail to patients’ homes, with content delivered more gradually, over an 8 month period, and in smaller educational increments using supplementary texts, postcards and, in one condition, telephone support from an educator (Table 1). Both *ET* and *ETH* were developed to encourage informed decision-making through a comprehensive explanation of the benefits and risks of dialysis, DDKT and LDKT.

**Table 1 Tab1:** Explore Transplant at Home mailed intervention materials

Module	Brochures	Fact Sheets	Postcards	Videos
1	Explore Transplant: A Guide for Family and Friends	Transplant or Dialysis Fact Sheet	Your Exploration of Kidney Transplant Begins at Home	Exploring Transplant
	Why People Donate Their Kidneys	Deceased or Living Donation Fact Sheet	Explore Transplant with Your Friends and Family	
	Why Kidney Patients Get Transplants		Learn How Life Can Improve After Transplant	
2	–	Recipient Evaluation, Surgery and Recovery Fact Sheet	Learn Something New About Receiving a Kidney	Kidney Recipients’ Transplant Experiences
		Possible Risks to Kidney Recipients Fact Sheet	Compare the Risks and Benefits of Transplants	
			Learn What Transplant Evaluation is Like	
3	–	Living Donor Evaluation, Surgery and Recovery Fact Sheet	Learn What it is Like to be a Living Donor	Living Donors’ Donation Experiences
		Possible Risks to Living Donors Fact Sheet	Learn Why People Want to Be Living Donors	
			Compare the Risks and Benefits of Living Donation	
4	Deciding What to Do	Kidney Disease Resources Fact Sheet	Weigh the Pros and Cons of All Your Options	Deciding What to Do
		Missouri Transplant Centers Fact Sheet	Consider Living Donation	
			Plan Your Next Steps	
Totals	4	8	12	4

A Medical Advisory Board including social workers, case managers, nephrologists, kidney patients, and experts in health education reviewed and approved all components of the *ETH* educational intervention to ensure its cultural sensitivity and that the needs of low-income and low health literacy groups were addressed.

### Missouri Kidney Program

This study features a partnership between [name] transplant research team and the Missouri Kidney Program (MoKP) [40]. Established in 1968 to serve and educate Missouri’s citizens with chronic kidney disease (CKD), MoKP subsidizes the costs of dialysis and transplant medication for low-income ESRD patients in Missouri, effectively operating as an insurance company would with respect to their 1,200 patient member group. MoKP also has strong, statewide partnerships with over 160 dialysis centers across the state of Missouri (Fig. 1) and fosters the exchange of medical, technical and administrative information among programs and professionals who treat patients in these dialysis centers.

**Fig. 1 Fig1:**
[figure not shown]
Intervention region: Missouri dialysis centers

### ETH Educational Components

#### Printed Materials

Many of the printed materials, including brochures and factsheets, used as part of the *ETH* education program are part of the original *ET* Program [19]. Every 8 weeks, within the educational intervention period, patients in the *ETH*-PG and *ETH*-EG intervention conditions will receive four educational print and video modules by mail. Transplant education postcards will also be mailed to patients every two weeks following the mailing of each of the four modules, for a total of 12 postcards over the course of 8 months.

#### Videos

As part of their mailings, patients will receive four *ET* DVD videos, averaging 20 minutes in length, to review at home with people who help them make important health decisions. If patients indicate that they do not have a DVD player at home, one will be provided to them as part of the trial. The videos include the stories of 20 transplant recipients and living donors, and discuss the questions and fears they had before getting a transplant and why they became motivated to pursue transplant. The health professionals in the videos provide answers to common questions, including specifics about transplant evaluation, surgery and recovery processes involved with being a transplant recipient or a living donor. All videos are closed-captioned for the hearing impaired.

#### Text Messaging

Text messaging has become a popular form of communication [41] and a common way to receive updates and important information quickly and conveniently [42]. Healthcare providers are now utilizing these short messages to deliver reminders to patients about appointments, prescription medications, and health education [43, 44]. In the United States, 89 % of households have access to a cell phone [45]. In 2011, 73 % of those who owned cell phones used them to send and receive text messages [46]. Thus, to increase the ways we can reach patients with educational messages, the *ETH* program has incorporated the use of text messages that contain recommendations, quiz questions, and educational facts that complement the printed materials and videos during each module. (Table 2). Patients in both *ETH* intervention conditions will have the option of enrolling in an educational text messaging service designed to supplement the *ETH* education they are receiving in the mail. Patients in the *ETH*-PG and *ETH*-EG conditions will receive a minimum of 67 messages. Those who respond to interactive messages, such as quiz questions, could receive up to 80 messages over the intervention period. Patients who opt into the text messaging are provided $10 remuneration to cover the cost of standard text messaging rates. Text messaging services are provided through Songwhale LLC, [47] an institutional review board approved partner.

**Table 2 Tab2:** Sample text messages

Text Message Type	Content
Recommendation	What does your family think about living donation as an option for you? Ask them! They know you the best and their opinions might help you decide.
Quiz	Can living donors who donate a kidney still have kids afterwards? Know the answer? Text back YES or NO.
Fact	Did you know? Nationally, most patients wait, on average, 4 years for a kidney from the deceased donor waiting list.

#### Transplant Educator

Patient support programs using health educators are increasingly being offered under health insurance plans [23] with staple components including patient assessment planning, facilitation, and advocacy [29, 48]. Though this intervention was not able to provide a comprehensive case management program, *ETH* has incorporated key tenets from case management models and created a telephone transplant educator whose goal is to guide patients through *ETH* to increase knowledge and informed decision-making (*ETH*-EG condition only). During a series of four calls, each lasting approximately 20 minutes, which will occur after each *ETH* module is mailed, the educator and patient will review the educational materials and discuss the risks and benefits of transplantation. The educator will also provide support by addressing patient concerns, problem-solving, and practicing empathetic listening. The transplant educator who delivers this intervention is a nephrology social worker who has had over 20 years of experience working with CKD patients. The educator has also received extensive training in the TTM and on how to administer *ETH*.

### Control Condition: Standard-of-Care

Patients randomized to the standard-of-care condition will not receive any educational materials from our program and will only participate in the survey portion of the investigation. The study team will conduct a phone survey to assess the actual educational practices occurring within each dialysis center by interviewing the dialysis providers who deliver transplant education. Research has shown that the most common educational practices in dialysis centers are recommending that patients learn more or be evaluated for transplant referring patients to an education program at a transplant center or kidney organization, and providing them with brochures one time [18]. Dialysis providers will be asked to continue their current practices throughout the study period without change. While Control patients will be free to ask additional questions or solicit more information from their dialysis educators at any point during the study period, no additional educational interventions will be delivered.

### RCT Overview

This RCT has three conditions with equal allocation of patients to each condition: (1) the control condition or standard-of-care; (2) the *ETH* Patient-Guided (*ETH*-PG) condition; and (3) the *ETH* Educator-Guided (*ETH*-EG) condition (Fig. 2). All enrolled patients will complete a baseline survey and a follow-up survey, 8 to 10 months post-baseline. We will recruit 540 patients at the start of the 8 month educational intervention period to complete the baseline survey, with 180 patients in each condition. After attrition, 150 patients in each condition (*n* = 450 total) are expected to complete the follow-up survey.

**Fig. 2 Fig2:**
[figure not shown]
Explore Transplant at Home study design

### Patient Recruitment Eligibility, and Retention

The sample for our study will be drawn from the MoKP patient roster plus additional patients from Missouri dialysis centers. To enroll in the RCT each subject must: (1) be 18–74 years of age, (2) self-identify as Black or White race, (3) currently be on dialysis, (4) have a household income at or below 250 % of the federal poverty level, and (5) be able to speak and read in English. Participants who meet any of the following exclusion criteria are not enrolled: (1) has a visual and/or hearing impairment that would preclude him/her from watching and reading educational study materials, (2) has had a previous kidney transplant, and/or (3) has previously been told that they are not a candidate for transplant.

Those who are transplant-eligible will be contacted directly by phone and via mailed letters, inviting them to participate in our trial. Additionally, Kilgore’s Pharmacy, contracted by the University of Missouri Health System to support patients who receive medication assistance through MoKP, will insert flyers advertising the *ETH* research study into patients’ prescription medication refills. After being informed of the risks and benefits of the trial, patients will be asked to give verbal informed consent to participate. If a patient agrees to participate, he or she will be randomized to one of the three educational conditions using an unrestricted (simple) random allocation sequence implemented within the trial’s data capture software, after they complete the baseline survey. The randomization sequence was created by a data manager using a random sequence generator, is stored in an encrypted spreadsheet, and is not accessible by the principal investigator. This protocol has been approved by the University of California, Institutional Review Board (#14-000802), the University of Missouri, Columbia Institutional Review Board (#00048966), and is registered at ClinicalTrials.gov (#NCT02268682).

### Survey Timepoints

#### Baseline Survey

Patients will complete a short phone screening (5 min.) to assess whether they meet the eligibility criteria and if so, are invited to participate, review the informed consent sheet with a surveyor, and then complete a 45-minute baseline survey. The survey assesses demographic, clinical and cultural factors, socioeconomic transplant derailers, baseline level of transplant knowledge, decisional balance, self-efficacy, and any steps they may have taken to learn about staying on dialysis, DDKT or LDKT. Patients will receive $25 for completing the baseline survey.

#### Follow-up Survey

After the intervention period (approximately 8–10 months post-baseline) a 35-minute follow-up survey will be completed over the phone to assess changes in patients’ level of transplant knowledge, decisional balance, self-efficacy, informed decision-making, decisional conflict, and any steps they may have taken to learn about staying on dialysis, DDKT, or LDKT. They will also complete a process evaluation about the helpfulness of the *ETH* program. Patients who are deemed ineligible for transplant or receive a transplant during the interim period between the baseline and follow-up surveys will be given only an abbreviated set of questions during the follow-up survey that excludes any questions about their pursuit of transplant. Patients will receive $50 for completing the follow-up survey.

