### Outcomes

#### Transplant Knowledge

Our primary outcome measure is level of DDKT and LDKT knowledge. Patients will be asked 17 true/false and 8 multiple choice questions about the basic facts, advantages, risks and outcomes of DDKT and LDKT to assess knowledge levels (e.g., “Transplant recipients are at risk of developing high blood pressure and high cholesterol,” “The transplant team will let a living donor back out from donating on the day of the surgery”).

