#### Small Steps toward DDKT and LDKT

Several action steps toward pursuit of both DDKT and LDKT will be assessed using validated measures (e.g., “Do you plan to call the transplant center to begin evaluation,” “Do you plan to share your interest in living donation with your family and friends?”) [50, 51], each of which the patient will report as having “already done,” “planning to do,” or “don’t plan to do.”

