#### Statistical Analyses

Where feasible and appropriate, multiple imputation will be used to account for missing data [60]. Multilevel random effects models (MRMs) will also be used to account for correlated data (dialysis center clustering and serial measurement). We will compare the characteristics of patients who refuse to join the study or are never successfully contacted to those who do not, as well as patients who drop-out to those who do not, to determine if the patient selection procedure has biased the sample.

We will compare the difference in mean knowledge change, change in self-efficacy, and change in decisional balance (baseline to follow-up survey) of participants in the 3 study arms using MRMs with normal outcome distributions. A MRM with a normal outcome distribution will also be used to test for mean differences in the Decisional Conflict Scale at 8 months post-baseline, and Rao-Scott χ^2^ tests adjusting for dialysis center clustering will be performed to test for differences in patients’ answers to the informed decision-making items on the follow-up survey: “I have all the facts I need to make an informed decision about whether to stay on dialysis/pursue DDKT/pursue LDKT” (agree/disagree). Rao-Scott χ^2^ tests will also be used to test differences in the proportion of patients in each condition who took each small step toward transplant (e.g., “Do you plan to share your interest in living donation with your family and friends?”), operationalized as the number who had not taken each step at baseline but had at follow-up.

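### The follow-up survey skips the pursuit questions for patients transplanted or ruled ineligible, leaving outcome-related blanks in the small-step outcome that no later analysis can fully recover

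*Protocol article*

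**What the plan says.** The rule is in the Follow-up Survey section of the protocol article. "Patients who are deemed ineligible for transplant or receive a transplant during the interim period between the baseline and follow-up surveys" receive a shortened interview; they "will be given only an abbreviated set of questions during the follow-up survey that excludes any questions about their pursuit of transplant".

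The outcome that needs those questions is set out in two places. Under Small Steps toward DDKT and LDKT, the data are patient reports on a list of actions, "each of which the patient will report as having “already done,” “planning to do,” or “don’t plan to do". Under Statistical Analyses, a success is "operationalized as the number who had not taken each step at baseline but had at follow-up", and Rao-Scott "tests will also be used to test differences in the proportion of patients in each condition who took each small step toward transplant". The steps also appear among the outcomes for the interaction models on heterogeneity of effect.

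The only stated provision for blanks is general: "Where feasible and appropriate, multiple imputation will be used to account for missing data". The article names no other source of step data and no coding rule for patients who were transplanted or ruled ineligible.

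On the standing of this outcome, the Background says "We will also explore which DDKT and LDKT action steps patients commonly take during an 8 month period", and the Outcomes section says "Our primary outcome measure is level of DDKT and LDKT knowledge".

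**The concern.** Whether a patient is asked about steps depends on something that happens after randomization and lies close to the outcome. The eligibility criteria exclude anyone with a previous transplant or already told they are not a candidate, so every event that triggers the short survey is new since enrolment. A transplant cannot happen without evaluation, and a ruling of ineligibility may follow from one. Calling the center to begin evaluation is one of the article's own example steps. A patient who makes that call after baseline and is then transplanted has taken the step, yet the data set holds no answer.

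If such patients are more frequent in one arm, the between-arm comparison of step proportions is distorted. This cannot simply be left to an analysis plan. The gap arises from what is asked on the telephone, and once the calls are made the answers do not exist.

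**Working it through.** **Plan's own figure.** The article gives no expected step rates, no transplant or ineligibility rates, and no power for the step outcome, so there is nothing to reproduce. The only figure used from it is the expected 150 completers per condition (RCT Overview). All rates below are assumptions for illustration.

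**Setup.** Let r be the share of an arm given the abbreviated survey, q the share of the remaining patients who newly take a step, and f the share of removed patients who newly took it, taken as equal in both arms.

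- True rate in an arm: r·f + (1 − r)·q
- Seen if removed patients are dropped: q
- Seen if they are imputed within arm at the rate of the rest: also q
- Seen if they are coded as not taken: (1 − r)·q

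**Main illustration.** ETH arm: r = 5%, q = 25%. Control: r = 2%, q = 20%.

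- True difference = (0.05f + 0.95 × 0.25) − (0.02f + 0.98 × 0.20) = 0.03f + 0.0415
- Seen, dropped or imputed: 0.25 − 0.20 = 5.0 points
- Seen, coded as not taken: 0.2375 − 0.1960 = 4.15 points

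| f | True difference | Seen if dropped or imputed | Error |
|---|---|---|---|
| 100% | 7.15 | 5.0 | −2.15 (30% of the true value lost) |
| 50% | 5.65 | 5.0 | −0.65 (11.5% lost) |
| 25% | 4.90 | 5.0 | +0.10 |
| 0% | 4.15 | 5.0 | +0.85 (overstated) |

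The sign changes where 0.03f + 0.0415 = 0.05, that is f = 0.0085/0.03, about 28%.

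**Heavier removal.** With 10% against 5% and the same q, the true difference at f = 100% is (0.10 + 0.90 × 0.25) − (0.05 + 0.95 × 0.20) = 8.5 points, against 5.0 seen.

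**Second set of assumed rates.** True rates of newly taking the step are 45% in ETH and 30% in control, a 15-point difference.

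- Removal 5% in both arms, all new step-takers: dropped, 0.40/0.95 − 0.25/0.95 = 15.8 points; coded as not taken, 15.0.
- Removal 10% against 5%, all new step-takers: dropped, 0.35/0.90 − 0.25/0.95 = 12.6 points; coded as not taken, 0.35 − 0.25 = 10.0.
- Removal 10% against 5%, none of them new because all had taken the step by baseline: dropped, 0.45/0.90 − 0.30/0.95 = 18.4 points; coded as not taken, 15.0.

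**Scale against noise.** In the main illustration the removed patients number 0.05 × 150 = 7.5 and 0.02 × 150 = 3 per arm. The standard error of the 5.0-point difference, ignoring clustering, is √(0.25 × 0.75/150 + 0.20 × 0.80/150) = √0.00232, about 4.8 points. The largest error in the table, 2.15 points, is a little under half of that.

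**Why imputation does not help.** No patient with the event has an observed follow-up step. Even with event status in the imputation model, the data cannot show how the event relates to the step. The model can only carry over the pattern of patients who are still eligible and on dialysis, whereas for a transplant recipient some answers are all but fixed by the transplant itself.

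**The case against.** The strongest reply is that this is a small gap in an exploratory outcome. The trial is powered on knowledge, and nothing shows that the abbreviated survey leaves out the knowledge items. That stands, and it limits the weight of the point.

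Several stronger readings are tempting, and the article does not support them.

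- *The loss differs by arm.* A reader might infer this because the article reports that the parent program increased pursuit of transplant, and that materials alone raised the start and completion of evaluation in a related trial. That makes a difference between arms plausible, but no rates by arm are given. With equal removal the distortion is slight (15.8 or 15.0 points against a true 15).
- *The bias is toward no effect.* This needs most removed patients to be new step-takers. Follow-up is 8 to 10 months, while the trial's own sample text message cites an average deceased-donor wait of 4 years. Many recipients may have taken the early steps before baseline and would not count as new. The bias can then run the other way.
- *The lost patients are the intervention's clearest successes.* That may fit some transplant recipients. It does not fit patients ruled ineligible, perhaps for medical reasons unrelated to the education.
- *The denominator dilutes the effect.* One could read the proportion as including patients who had already taken the step at baseline. The wording does not clearly fix the denominator, and a proportion of all randomized patients is still a valid randomized comparison. The gain from restricting it, about 47% to 56% power, rests wholly on assumed rates. It is not part of this point.

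It can also be said that transplant status must be known at follow-up, so an analysis plan could code the steps a transplant requires, and that the imputation clause is conditional and does not commit to imputing these patients. Both are true but incomplete. Coding cannot settle steps that a transplant does not entail, such as whether a deceased-donor recipient raised living donation with family. It settles nothing for patients ruled ineligible.

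**Conclusion.** The point holds in limited form. As written, the survey rule removes the data that the small-step outcome needs for patients whose missing answers are closely tied to that outcome, and the stated missing-data method would not restore them. The comparison can be biased if transplant or ineligibility differs by arm. In the main illustration the error runs from 2.15 points too low to 0.85 too high around a seen difference of 5.0. Those figures assume 5% and 2% removal, 25% and 20% step-taking among the rest, the same f in both arms and no clustering. Neither the size nor the sign can be learned from the article, or later from the data if the questions are not asked.

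The effect is confined to the exploratory step outcome and the interaction analyses that use it. The primary knowledge comparison is not shown to be affected. This is a change worth making before follow-up calls begin, not a threat to the trial's main conclusion.

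**What to change.** 1. Keep the already-done step items in the abbreviated survey, worded to cover the time up to the transplant or the ineligibility decision. The planning items can still be skipped.
2. As a minimum, set a coding rule before analysis: for a transplant recipient, each step that a transplant necessarily entails counts as taken if it had not been taken at baseline.
3. Do not impute step items for these patients as if they were still eligible and on dialysis.
4. Report the numbers transplanted and ruled ineligible by arm, alongside the step results.
5. Add a sensitivity analysis for ineligible patients, from all counted as having newly taken the step to none.

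The cost is a few branching items, slightly longer calls for a small number of patients, and one coding rule. Item 1 must be in place before the follow-up interviews; items 2 to 5 can be settled any time before analysis.
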